### Social network analysis

A network is a structure made up of nodes (individuals, organisations, etc) that are connected together by ties (relations such as friendship, kinship, exchanges, activities, etc) [53-55]. Social network analysis provides a way of characterising and investigating such structures, including through network visualisation (using graphic display as illustrated in Figure 2), structural analysis and statistical analysis [55-58]. If participants' networks influence smoking behaviours, it would be expected that participant’s networks would share similar smoking behaviours. Thus, we would compare the observed network to a simulated network with the same network characteristics, including the same overall rate of smoking prevalence, but with the incidence of smoking randomly distributed across the network [59]. If clustering is occurring among smokers or non-smokers, then the probability that a participant who smokes has a network contact who is also a smoker should be higher in the observed network than in the simulated network [21,60]. Perceived proportion of peers who smoke will be measured by analysing the respondents’ perceptions of how many of their peers smoke (about what proportion (%) of your friends and acquaintances use tobacco?) and respondents’ perceptions of how many of their five closest friends and family are regular smokers (thinking about your five closest friends and family, how many of these five are regular smokers?).

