Social network analysis will be used to assess if individuals' social networks influence smoking behaviours. Network analysis will include exploring smoking and non-smoking networks constructed from the survey data and complemented by the qualitative data collection. This will include network visualization, structural analysis and statistical analysis [55]. Several network level measures of structure will be assessed, including clustering, network size, number of ties and reciprocity [55,58]. To study the clustering of smoking behaviour, we will compare the observed network at each data collection point to a simulated network with the same network characteristics, including the same overall rate of smoking prevalence, but with the incidence of smoking randomly distributed across the network [59]. If clustering is occurring among smokers or non-smokers, the probability that a participant who smokes has contact with other smokers should be higher in the observed network than in the simulated network [21,60]. These network metrics will be used to provide a descriptive presentation of the network/s and any changes over time. The pre- and post-test survey will be analysed using Analysis of Variance (ANOVA) on the gain scores and Analysis of Covariance (ANCOVA).

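### The clustering comparison names a single simulated network and a bare excess as its sign of clustering; read literally, it has no error control

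*Protocol article*

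**What the plan says.** The comparison appears twice in the protocol article.

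- Background, Social network analysis: "we would compare the observed network to a simulated network with the same network characteristics, including the same overall rate of smoking prevalence".
- Methods/design, The survey, Analysis: "we will compare the observed network at each data collection point to a simulated network with the same network characteristics". The null model is described as "including the same overall rate of smoking prevalence, but with the incidence of smoking randomly distributed across the network".

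The Analysis section then states the expected pattern. It opens with "If clustering is occurring among smokers or non-smokers" and continues: "the probability that a participant who smokes has contact with other smokers should be higher in the observed network than in the simulated network". The Background section says the same in nearly the same terms.

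The purpose is given at the start of that part of the Analysis section: "Social network analysis will be used to assess if individuals' social networks influence smoking behaviours". Its later description of how the metrics will be used is milder: "These network metrics will be used to provide a descriptive presentation of the network/s and any changes over time".

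Neither section gives a number of simulations, a reference distribution, a margin or a cut-off for this comparison. The chi-square, t, rank and regression methods listed earlier under Analysis are not tied to it.

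**The concern.** One random placement of smoking on a network is one draw from the distribution expected when there is no clustering. If the observed network also has no clustering, it is another draw from that same distribution, so which of the two is larger is a matter of chance. A comparison made this way cannot separate clustering from its absence, because nothing in it says how large an excess must be before it means anything.

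This comparison carries much of the quantitative evidence on whether people's networks affect their smoking. The article already expects similar behaviour within networks (Background, Social network analysis), so a chance excess could easily be taken as confirmation. The comparison is also repeated at two waves about 12 months apart, and changes over time are to be described. If each wave is set against its own single draw, part of any change between waves is produced by the simulation and not by the community.

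**Working it through.** The article states no error rate or number of simulations here, so there is no figure of its own to reproduce.

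**Inputs from the article.** Network size 102 (the minimum in the survey Sample size section). Smoking prevalence 36% (same section), with the 46% national daily rate from the Background as a second setting. Two waves.

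**Inputs assumed.** The article gives no tie density. Two kinds of network were used:
- Random networks with a mean of 3 or 5 ties per person.
- Grouped networks: 15 groups of 6 or 7 people, tie probability 0.6 within a group and sparse ties between groups.

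**Statistic.** The share of smokers' ties that lead to other smokers.

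**Step 1, by reasoning.** Hold the ties and the number of smokers fixed. With no clustering, the observed statistic and the statistic from one random re-allocation have the same distribution and are exchangeable. Hence

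P(observed > simulated) = (1 − P(tie)) / 2,

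where a tie means that the two values are equal. With P(tie) between 0.1% and 0.7%, this is (1 − 0.001)/2 = 0.4995 down to (1 − 0.007)/2 = 0.4965. The result does not depend on network density.

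**Step 2, by simulation.** There were 4,000 replicates in each of 8 settings (2 densities × 2 network types × 2 prevalences), with smoking placed at random. The Monte Carlo standard error near 0.5 is √(0.5 × 0.5 / 4,000) = 0.008.

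| Reading of the comparison | How often it signals clustering when there is none |
|---|---|
| Above one simulated network | 0.487 to 0.510 |
| Above the mean of 499 simulated networks, any excess counted | 0.491 to 0.510 |
| One-sided permutation p ≤ 0.05 against 499 re-allocations | 0.048 to 0.055 |

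The second row shows that more simulations alone do not help. The missing cut-off matters as much as the single draw.

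**Step 3, simulation noise.** Across the 8 settings, the SD of one random draw of the contact probability was 0.038 to 0.060, or about 0.04 to 0.06. If each wave uses its own independent draw, the two draws alone add an SD of √2 × 0.04 = 0.057 to √2 × 0.06 = 0.085 to the change in the gap between waves, however closely the observed networks at the two waves are related.

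**Step 4, what a cut-off would require.** By the normal approximation, the 95th percentile lies about 1.645 × 0.04 = 0.066 to 1.645 × 0.06 = 0.099 above the simulated mean.

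**The case against.** The strongest reply is that the article does not state the rule just tested. It says that clustering, if present, should produce a higher value. It does not say that a higher value will be declared clustering. The singular noun may simply name a null model, and no sentence says that one draw will be made. The method is cited to outside sources, statistical analysis is listed among the network methods, and the metrics are called descriptive. A journal article may also leave the number of simulations and the threshold to a fuller document.

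Much of this stands. The rule is inferred, and an omitted simulation count would not be a finding in itself. But the article does more than omit detail: it states a comparator and a direction in both places and offers no other criterion. The comparison serves its stated purpose only if an excess is taken as evidence of clustering. Calling the result descriptive does not remove the noise in a gap measured against one random draw.

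Two stronger readings are tempting and are not supported:

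- A reader might infer a still higher error rate by counting a signal at either wave, or among either smokers or non-smokers. The article states no either-wave rule. The only quantity it defines is the smoker-contact probability; non-smokers appear only in the conditional clause.
- A reader might infer that the whole answer to the first research question rests on this comparison. The article also plans perceived peer smoking, structural network measures, interviews and focus groups, combined by triangulation.

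**Conclusion.** The point holds as a defect of wording in a stated method. Followed literally, the comparison shows an excess about half the time at each wave when smoking is not clustered, and the size of the gap is partly noise. The 50% rests only on exchangeability under random placement and on the literal reading of both sections. The SD of about 0.04 to 0.06 rests on 102 people and the assumed networks, and would differ at other densities. The documents do not show that the investigators will in fact draw only one network or declare clustering from any excess, so this is a request to fix the text and not a finding that the analysis will be done wrongly.

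**What to change.** In both sections (Background, Social network analysis; and The survey, Analysis), replace the single simulated network with many, for example at least 1,000. Each should keep the observed ties and the observed number of smokers and re-allocate smoking at random. At each wave, report the observed smoker-contact probability with the simulated mean and 95% range. Read it as clustering only if it exceeds the 95th percentile of the simulated values (one-sided permutation p < 0.05).

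The cost is a change of wording and a little computing on data already planned; no further participants are needed. The small downside is that weak clustering, in these settings an excess below roughly 7 to 10 percentage points, would no longer be read from direction alone.

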### Homophily

Individuals' social networks can be homogeneous with regard to socio-demographic characteristics, intrapersonal factors or behaviours, such as smoking; “similarity induces homophily” [70]. Homophily is the principle that interaction between similar individuals or organisations occurs more frequently than among dissimilar individuals or organisations [70]. This is related to the process of peer socialisation, whereby people take on the values and behaviours of the ‘group’ in order to be accepted [71]. In the context of the social norms around tobacco among Indigenous Australian people and the high rate of smoking, homophily is a sound underpinning for this research. McPherson and colleagues [70] indicated that behavioural, cultural, genetic or other information that flows through networks is more likely to be clustered. In alignment with the theory of triadic influence, this may be one factor for the inconsistent effect of tobacco control on smoking rates of different population groups [70].

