#### The sample population

Participants will generally be Indigenous Australian people residing in the ACT region. The sample will include adults and children (12 years and above). Young people have been included to reflect the younger Indigenous Australian demographic profile and the early uptake of tobacco use in children [95,96].

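### The network comparison can show that smokers cluster, but it cannot show that networks influence smoking, the question it is assigned

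*Protocol article*

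**What the plan says.** The first research question, given under Research questions and again under Aim and objectives, is whether social networks influence smoking behaviours. The survey Analysis section hands it to one method: "Social network analysis will be used to assess if individuals' social networks influence smoking behaviours".

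The comparison is then described in that section: "we will compare the observed network at each data collection point to a simulated network with the same network characteristics". The simulated version also keeps the observed prevalence of smoking, "but with the incidence of smoking randomly distributed across the network". The expected sign of clustering is that "the probability that a participant who smokes has contact with other smokers should be higher in the observed network than in the simulated network". The network metrics, and any change in them over time, are to be presented descriptively.

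The Background section on social network analysis gives the reasoning: if networks influence smoking, "it would be expected that participant’s networks would share similar smoking behaviours", and the comparison follows from that. The Homophily section adopts a second theory: "Homophily is the principle that interaction between similar individuals or organisations occurs more frequently than among dissimilar individuals or organisations". It says that networks can be alike in socio-demographic characteristics and in smoking itself. The sample runs from age 12 upwards (The sample population), and recruitment is by convenience and snowball sampling.

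**The concern.** The question is causal and the comparison is not. Placing smoking at random over a fixed network gives a reference that is beaten whenever smokers are connected to smokers more often than chance predicts. Three mechanisms do this:

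- contacts change each other's smoking (influence);
- people choose contacts who smoke as they do (homophily on smoking);
- a third attribute, such as age, shapes both ties and smoking.

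The comparison gives the same answer for all three. The protocol names the second and allows for the third, but nowhere says how influence would be told apart from them. Homophily is linked to peer socialisation instead, and the Limitations do not mention the problem. Matching the simulated network on its other characteristics does not help as described, because smoking itself is reallocated and no conditioning on age or household is stated.

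The two waves could help with time order, but each is compared separately. None of the other planned analyses (multiple regression, gain-score ANOVA, ANCOVA) is described as relating contacts' earlier smoking to a person's later smoking.

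At stake is what can be concluded on the first research question. The Conclusions say the results may inform the design of programs and policies.

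**Working it through.** The protocol gives no figure for this comparison, so there is none to reproduce. The check asks how often the described comparison signals clustering when no one influences anyone.

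**Inputs from the protocol:** 102 people and 36% prevalence (Sample size), used only as network size and smoking level; the reference and the statistic as described.

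**Assumed inputs, not in the protocol:** mean of five contacts; one-third of the sample young; 5%, 12% or 20% of the young smoking; the tie-preference weights; a one-sided 5% test with 499 random reallocations and 500 data sets per setting.

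**Adult rate.** To keep 36% overall, the adult rate is (0.36 − p/3)/(2/3), where p is the rate in the young. This gives 51.5%, 48% and 44% for p = 5%, 12% and 20%.

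**Meaning of the weights.** A same-age pair is w times as likely to be tied as a cross-age pair. With 34 young and 68 adults there are 561 young pairs, 2,278 adult pairs and 2,312 mixed pairs. The share of young people's ties that go to the young is about 2w·561/(2w·561 + 2,312): 33%, 49%, 66% and 80% for w = 1, 2, 4 and 8.

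**One setting by hand** (p = 12%, w = 4):

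- Weighted pairs: 2,244 young, 9,112 adult, 2,312 mixed; total 13,668.
- Both ends smoke: (2,244 × 0.0144 + 9,112 × 0.2304 + 2,312 × 0.0576)/13,668 = 0.166.
- A given end smokes: (2,244 × 0.12 + 9,112 × 0.48 + 2,312 × 0.30)/13,668 = 0.390.
- Probability that a smoker's contact smokes: 0.166/0.390 = about 0.42.
- Random reference: with 0.36 × 102 = 36.7 smokers, (36.7 − 1)/101 = 0.35.

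The simulation gives the same pair, 0.42 against 0.35, with no influence present.

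**Share of data sets in which the random reference is rejected, zero influence throughout:**

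| Setting | Rejected |
|---|---|
| No age gradient, no tie preference | 4.0% |
| Age gradient (12% of young smoke), ties ignore age | 4.6% |
| 5% of young smoke; w = 2, 4, 8 | 33%, 68%, 85% |
| 12% of young smoke; w = 2, 4, 8 | 24%, 47%, 56% |
| 20% of young smoke; w = 2, 4, 8 | 14%, 24%, 25% |
| No age gradient; same-smoking-status weight 1.25, 1.5, 2 | 29%, 69%, 96% |

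The first two rows show that the procedure holds its level when there is no clustering. In the other rows the clustering is real, so rejection is correct as a statement about clustering. It would be wrong only as a statement about influence.

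**The case against.** The survey Analysis section already introduces the comparison as a study of clustering and calls the metrics descriptive. A reader might infer that the protocol commits itself to declaring influence whenever the random reference is beaten. It does not: the Background argues that influence would produce similarity, and no section states the reverse as a decision rule. This stands, and it narrows the point to a mismatch between the assigned question and the comparison.

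The network analysis is also not alone. Interviews and focus groups explore family and peer influence, perceived peer smoking is asked directly, and triangulation is the declared strategy. This stands too, but none of these is described as a quantitative peer-influence analysis.

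A reader might further infer from the upper figures that a positive result is almost certain, or that age groups mainly name their own age. The documents support neither. They give no age-specific rates or tie patterns, and the network questions cover family and household members, whose ties can cross ages.

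Finally, the exact attributes held fixed in the simulated network may sit in a fuller plan. That excuses missing detail. It does not excuse assigning a causal question to a comparison whose stated reference leaves smoking random over the whole network.

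**Conclusion.** The point holds in a limited form. As described, the comparison can establish clustering of smoking at each wave. It cannot separate influence from homophily or shared attributes, and no other stated analysis does so. That conclusion is logical and needs no simulation.

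The size is illustrative. Under the assumed inputs and zero influence, the nominal 5% test rejects in about 5% of data sets if ties ignore age, 14% to 85% with same-age tie preference, and 29% to 96% with same-status preference. Age contributes only if smoking differs by age and ties are age-assortative. The protocol states no significance level for this comparison, so the 5% test is itself an assumption. The pre/post comparison on which the sample size rests is unaffected.

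**What to change.** 1. **Restrict the reference.** Permute smoking status within age band, and within sex or household where numbers allow, many times. Clustering is then judged beyond those shared characteristics. In one separate run with strong age structure (30% young, 5% of them smoking, 85% of their ties to the young), rejection fell from 70% to 3%. This does not remove selection of contacts on smoking itself.
2. **Use the two waves.** Fit a logistic regression of wave-2 smoking on own wave-1 smoking and the wave-1 share of contacts who smoke, adjusted for age and sex. The survey already asks how many of the five closest friends and family smoke. Report the result as temporal association, because homophily on unmeasured traits remains. This needs individuals linked across waves, which the panel survey in the Abstract and the gain scores imply.
3. **Align the wording.** State in the first research question and in the opening sentence on network analysis that the single-wave comparison addresses clustering or association. Add homophily versus influence to the Limitations.

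The cost is analysis text and some programming. The items needed are already planned, and the study is prospective, so the change can be made in advance. The downside is that with about 102 people the lagged estimate will be imprecise and the claim about networks more modest.

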Wellman [61] outlined that individuals’ behaviour is best predicted by examining their social network and ecological characteristics in which they are entrenched; not intrinsic factors such as attitudes, drivers or demographic characteristics. Furthermore, nothing can be accurately understood in isolation or without context [61]. Therefore, these structures―social networks of interconnected individuals―and characteristics can be useful to develop, tailor and implement health promotion and public health programs, including tobacco control [62]. Within the Indigenous Australian context, tobacco was seen as a prestigious substance and has been a highly valued commodity [3,7,63]. Smoking has been a central mechanism for relationships, assisting to maintain and reinforce kinship bonds and social relationships and also used as a practical currency and an incentive prior to Indigenous Australian peoples full engagement with the cash economy in the late 1960s [4-6]. As a result, the primary data collection in this study is expected to reflect the importance of social and cultural norms regarding smoking and the influence of social networks. It is anticipated that similar behaviours and beliefs about smoking will resonate among participant networks [23-25].

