#### Sample size

A minimum sample size of 102 participants was determined. This sample size is sufficient to obtain 90 per cent power to detect a 10 per cent reduction in smoking between the pre-intervention group (36%) when compared with the post-intervention group. The current population smoking rate is based on data obtained from the 2008 National Aboriginal and Torres Strait Islander Social Survey (NATSISS) relating to the ACT Indigenous Australian population [87].

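### Clustering is judged from smokers' contacts alone: this is sound if smokers and non-smokers have equally many ties, misleading if they do not, and less sensitive than also using non-smokers' contacts

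*Protocol article*

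**What the plan says.** The survey *Analysis* section of the protocol article fixes both halves of the comparison.

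- **Reference.** At each wave, what was observed is set against "a simulated network with the same network characteristics, including the same overall rate of smoking prevalence". Ties and prevalence are therefore kept as they are, and only the placing of smoking changes: "but with the incidence of smoking randomly distributed across the network".
- **Criterion.** The sign to look for is that "the probability that a participant who smokes has contact with other smokers should be higher in the observed network than in the simulated network". The condition this sign is meant to reveal is worded for both groups: "If clustering is occurring among smokers or non-smokers".

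The Background section *Social network analysis* gives the same criterion: "the probability that a participant who smokes has a network contact who is also a smoker should be higher in the observed network".

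No quantity for non-smokers' contacts enters, although the criterion is meant to reveal clustering in either group. The number of ties is planned only as an overall measure: "Several network level measures of structure will be assessed, including clustering, network size, number of ties and reciprocity". The *Analysis* section then says that the network metrics serve to describe the networks and their change over time. It states no test level and no p-value for this comparison.

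**The concern.** Scattering smoking at random over a network breaks any link between smoking and number of ties. The real network may have such a link. If smokers hold or receive more ties, everyone's contacts include more smokers, and that applies to non-smokers too. The smokers' figure then exceeds the simulated one although like does not seek like. If smokers are less connected, the shift goes the other way and offsets real clustering. Non-smokers' contacts would tell these cases apart, but the stated criterion does not use them.

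The comparison serves the first research question, whether social networks influence smoking. A high value could mean only that smokers are better connected, and an unremarkable one only that they are less so. Because the comparison is made at both waves, a shift in relative tie counts could also look like a change in clustering.

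**Working it through.** The article states no figure for this comparison, so there is none to reproduce.

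**Inputs from the article.** Smoking prevalence of 36%, from the survey *Sample size* section ("10 per cent reduction in smoking between the pre-intervention group (36%) when compared with the post-intervention group"), and 102 participants from the same section. This gives 37 smokers (0.36 × 102 = 36.7).

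**Assumptions, not in the article.** Tie counts or naming rates by smoking status; 5 named contacts each in the nomination networks; strength of homophily (the factor by which same-status ties are favoured); a one-sided 5% permutation test.

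**Step 1: reference value.** With smoking shuffled over a fixed network, a smoker's contact is a smoker with probability about (37 − 1)/(102 − 1) = 0.356, close to the prevalence. Keeping the whole network fixed does not change this, because it is the smoking labels that move.

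**Step 2: observed value without clustering.** Let p be the prevalence, and dS and dN the mean ties of smokers and non-smokers. The share of contacts who smoke is then the same for smokers and non-smokers:

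p·dS / (p·dS + (1 − p)·dN)

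This equals p only if dS = dN. At p = 0.36 and 8 against 6 ties it is 36×8/(36×8 + 64×6) = 288/672 = 42.9%. Other cases:

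| Ties, smokers / non-smokers | Share of contacts who smoke, no clustering |
|---|---|
| 5 / 5 | 36.0% |
| 6 / 4 | 45.8% |
| 7 / 4 | 49.6% |
| 4 / 6 | 27.3% |
| 3 / 6 | 22.0% |

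**Step 3: simulation, 5 named contacts each.** Labels were permuted on the observed network, 199 or 299 times per replicate. *Planned* is the smokers-only share. *Contrast* is smokers' share minus non-smokers' share under the same relabelling. Ranges cover separate runs.

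| Scenario | Planned flags | Contrast flags |
|---|---|---|
| No clustering, equal naming | 4–5% | 3–5% |
| No clustering, smokers named 7/6 as often | 21–26% | 4–7% |
| No clustering, 8/6 | 55–62% | 4–7% |
| No clustering, 9/6 | 80–84% | 4–7% |
| Clustering (factor about 1.4), equal naming; about 44% v 30% of contacts smoke | 67–69% | 96–97% |
| Clustering (factor about 1.4), smokers named 6/8 as often; 37% v 24% | 8–10% | 94% |

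**Step 4: simulation, mutual ties.**

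| Scenario | Planned flags | Contrast flags |
|---|---|---|
| No clustering, 5/5 ties | 4.8% | 5.2% |
| No clustering, 6/4 (45.7% v 46.3% of contacts smoke) | 74.5% | 5.0% |
| No clustering, 7/4 | 94.2% | 5.0% |
| Clustering (factor 2), 5/5 | 99.5% | 100% |
| Clustering (factor 2), 4/6 | 87.2% | 100% |
| Clustering (factor 2), 3/6 (42.5% v 16.3%) | 44.0% | 99.8% |

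**Step 5: alternative reading.** If the criterion means having at least one smoking contact, the pattern is the same in the mutual-tie networks: false flags of 60% at 6/4 and 86% at 7/4, and detection of 0% at 3/6 with factor 2.

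**The case against.** The strongest case against has five parts.

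- **The error is conditional.** It arises only if tie counts differ by smoking status, and the article gives no such counts. With equal ties the comparison holds its level, and with strong homophily a deficit of 4 against 6 ties still leaves 87% detection. This stands. A reader might infer that the statistic is simply invalid; the documents do not support that.
- **The article does not predict unequal ties.** A reader might take "Smoking has been a central mechanism for relationships, assisting to maintain and reinforce kinship bonds and social relationships" as saying that smokers are better connected. The sentence is about bonds and is largely historical, and the paragraph goes on to expect similar behaviour within networks. It gives neither a difference in tie counts nor a direction. It makes the question reasonable and does not answer it.
- **The error rates belong to an added test.** The article sets no level and calls the metrics descriptive. This stands: the percentages show how far the comparison can mislead and are not operating characteristics of the plan. A descriptive comparison with an unsuitable reference can still be misread.
- **Other evidence bears on the first question.** Respondents report the share of friends and acquaintances who use tobacco and how many of their five closest friends and family smoke regularly. Bivariate tests by smoking type and multiple regression are also planned. This stands, so the first research question does not rest on this statistic alone. The article does not, however, name the comparison of smokers' with non-smokers' contacts.
- **An article condenses.** Detail of the simulation may sit elsewhere. But the quantity and the reference are both stated, in two places, and the point concerns those.

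**Conclusion.** The point holds in conditional form. The stated criterion compares smokers' contacts with a reference near the overall prevalence. It therefore mixes clustering with any difference in connectedness between smokers and non-smokers. The direction follows from the algebra: more ties among smokers push towards apparent clustering, and fewer push towards hiding it.

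The size in this study is unknown. Under the assumed networks without clustering, false signals run from about 5% with equal ties to 55–62% when smokers are named 8/6 as often. Under moderate clustering with smokers named 6/8 as often, detection falls to 8–10%, against 94% for the contrast.

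With equal ties nothing is wrong with validity, but sensitivity is lost: about 69% against 96% under moderate homophily. That loss depends on the assumed strength; in the mutual-tie networks with factor 2 it nearly vanishes (99.5% against 100%).

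Reading this as a defect that defeats the first research question would go too far, given the descriptive role of these metrics and the other planned evidence. It is a free improvement to the analysis, not a must-fix.

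**What to change.** In the Background section *Social network analysis* and the survey *Analysis* section:

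- Replace the smokers-only probability by the difference (or odds ratio) between smokers and non-smokers in the share of contacts who smoke.
- Compare it with the same relabelled networks, not with zero. With 37 smokers among 102 people, random labelling alone gives a difference of about 36/101 − 37/101 = −0.010.
- Report mean number of ties by smoking status beside it at each wave, so that a shift in connectedness can be told from a change in clustering.

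The cost is about one sentence in each place. The data and the simulations are those already planned.
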